### Randomization

The randomization code is generated by the CTU ensuring that treatment assignment is unbiased and concealed from patients and investigator staff. Randomization is performed, stratified by site and by sex, in blocks of variable length in a ratio of 1:1. The block lengths are documented separately and will not be disclosed to the sites. The randomization code is produced by validated programs based on the Statistical Analysis System (SAS) and inserted into the secuTrial^®^ system.

### Statistical analysis

The primary estimand that corresponds to the primary trial objective “comparison of the efficacy of ATRA versus placebo as add-on to the backbone treatment DAC + VEN with respect to OS” is specified by the following 5 attributes (according to ICH E9 (R1)).

Population: Newly diagnosed AML patients as defined by the before mentioned inclusion and exclusion criteria randomized to one of the treatment arms (experimental vs. control) who received at least one dose of study treatment. The population will be called full analysis set (FAS).

Treatment: The randomized experimental arm backbone treatment DAC + VEN and IMP ATRA is compared to the randomized control arm backbone treatment DAC + VEN and Placebo regardless of dosing modifications, treatment interruptions, treatment discontinuation, regardless of intake of additional medications, and regardless of treatment with HCT.

Endpoint: OS defined as time from the date of randomization to the date of death from any cause. For patients surviving the time under observation in the trial, the time from the date of randomization to the date of the last follow up (visit or phone call) will be analyzed as censored observation.

Intercurrent events: Dosing modifications, treatment interruptions, discontinuation of the study treatment, intake of additional medications, treatment with HCT will be ignored. This corresponds to the treatment policy strategy according to ICH E9 (R1).

Population-level summary: The population-level summary is defined by the following statistical analysis approach. A Cox regression model being stratified for site and including, in addition to the effect of ATRA, sex as covariate for adjustment will be used. As estimate of the effect size, the hazard ratio (ATRA vs. placebo) will be calculated with corresponding two-sided 95% confidence interval. Superiority of ATRA vs. placebo will be tested from this model using the Wald test at one-sided level alpha of 2.5%. OS rates will be estimated by the Kaplan-Meier method by randomized treatment.

The estimands corresponding to the secondary trial objectives and endpoints are specified accordingly in the clinical trial protocol. The analysis of the treatment effects with respect to objective best response (CR, CRi, MLFS or PR) and with respect to CR_MRD-_ at least at one of the time points (after cycles 2, 4, or 6) will be performed with logistic regression models including, in addition to the effect of ATRA, site and sex as covariates for adjustment. As estimate of the effect sizes, the odds ratios (ATRA vs. placebo) will be calculated with corresponding two-sided 95% confidence intervals.

For evaluating QOL, EORTC QLQ-C30 scores will be calculated according to Fayers et al., 2001 [23], and the FACIT Fatigue scale will be calculated according to FACIT Administration and Scoring Guidelines [24]. At the different time points during follow-up changes in relation to baseline will be calculated. With respect to the secondary endpoints QOL, the treatment groups will be compared descriptively.

Safety is analyzed in the safety population including all randomized patients who received at least one dose of study medication, and according to the received treatment. AEs are coded using Medical Dictionary for Regulatory Activities (MedDRA). The probability of AEs defined by preferred term (PT) according to MedDRA and of AEs defined by system organ class (SOC) according to MedDRA will be estimated by the Aalen-Johansen estimator. For this purpose, the time from start of the first ATRA/placebo intake to the first occurrence of the specific type of AE (defined by PT or defined by SOC) will be analyzed. For patients not experiencing the specific type of AE, the time to the end of the documentation period or death, whatever occurs first, will enter the analysis and will be treated as a competing event. This will result in probability estimates (cumulative incidences) for the different AE types (defined by PT and by SOC) over time. The results will be displayed in summary tables by showing the cumulative incidences at the maximum observation time.

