## Methods/design

### Study design and setting

This is a prospective, randomized, double-blind, placebo-controlled, parallel group, multicenter phase III trial. The primary objective of the trial is to compare the efficacy of all-*trans* retinoic acid (ATRA) versus placebo as add-on to the backbone treatment (DAC + VEN) in older and unfit AML patients with respect to OS. Secondary objectives are to compare ATRA *versus* placebo as add-on to the backbone treatment (DAC + VEN) with respect to objective best response, i.e. CR/CRi/MLFS/PR, CR with negative measurable residual disease (MRD), probability of survival with objective best response, quality of life (especially fatigue) and safety.

Trial sites are located in Aachen, Augsburg, Berlin-Buch, Berlin-Neukölln, Bochum, Bonn, Braunschweig, Düsseldorf, Eschweiler, Esslingen, Freiburg, Hagen, Halle, Hannover, Heidelberg, Jena, Karlsruhe, Kleve-Goch, Lahr, Lübeck, Lüdenscheid, Mannheim, Münster, Oldenburg, Rostock, Saarbrücken, Trier, Ulm and Villingen-Schwenningen.

The study received approval from the competent authority and ethics committees of the University of Freiburg as well as the respective local ethics committees and was successfully submitted to the CTIS. Patient’s written consent to participate in this clinical trial and translational research program was obtained prior to any study-specific procedures. The identifying number of the DECIDER-2 trial in the German clinical trials registry is DRKS00023646 and in EU clinical trials register 2020-005495-36/2023-507461-26-00.

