### Sample size

Sample size calculation is based on the primary endpoint OS. The study should have a power of 80% to demonstrate superiority of ATRA vs. placebo with respect to OS at one-sided level alpha of 2.5% under the assumption of a hazard ratio of 0.67. This requires the observation of 191 deaths. A hazard ratio of 0.67 would correspond e.g. to a median OS time of 12 months vs. 8 months. The median OS time of 286 patients treated with AZA plus VEN 400 mg in the VIALE-A trial by DiNardo et al. (2020) [5] was reported as 14.7 months, in the control group of 145 patients treated with AZA plus placebo it was reported as 9.6 months (hazard ratio 0.66, 95% confidence interval [0.52, 0.85], *p* < 0.001 of VEN vs. placebo). In the DECIDER trial, the median OS time of 96 patients treated with DAC+ATRA (+/- valproate) was 8.2 months, and of 104 patients treated with DAC (+/-valproate) was 5.1 months, with a hazard ratio of 0.65, 95% confidence interval [0.48,0.88], *p* = 0.006 of ATRA vs. no ATRA [6].

Thus, the assumption of median OS times of 12 vs. 8 months for the planned trial seems to be realistic. Under this assumption, and a planned recruitment period of 3 years and an additional follow-up period of 1 year, it is necessary to include 230 patients (nQuery Advisor 7.0). If longer median OS times were observed (e.g. 15 vs. 10 months, also corresponding to a hazard ratio of 0.67), the follow-up period had to be extended to 1.5 years, in order to observe the required number of 191 deaths with the same number of included patients. To account for the possibility of up to 10% of the patients with incomplete follow-up, 230/0.9 = 256 patients will be randomized in total (ratio 1:1).

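### The 191 deaths match an unstratified calculation, but the primary Cox test is stratified over 29 small sites and has about 70% power at 191 deaths, or about 73–77% with all 256 patients followed

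*Protocol article*

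**What the plan says.** - Sample size section: "The study should have a power of 80% to demonstrate superiority of ATRA vs. placebo with respect to OS". The test is one-sided at 2.5%, and the assumed hazard ratio is 0.67. The event count follows: "This requires the observation of 191 deaths". The effect is illustrated by medians: "A hazard ratio of 0.67 would correspond e.g. to a median OS time of 12 months vs. 8 months". With "a planned recruitment period of 3 years and an additional follow-up period of 1 year, it is necessary to include 230 patients"; a 10% allowance for incomplete follow-up raises this to 256 randomised. The section mentions neither strata nor an allowance for site.
- Statistical analysis section, population-level summary of the primary estimand: the model is "A Cox regression model being stratified for site", with sex as a covariate. Superiority is decided by the Wald test from that model at one-sided 2.5%. No pooling of small sites is stated.
- Study design and setting section: the list that begins "Trial sites are located in Aachen, Augsburg, Berlin-Buch" names 29 sites.
- Randomization section: allocation is stratified by site and sex, in blocks of variable length, 1:1.
- Study treatment and procedures section: patients are followed until 12 months after the last patient is randomised.

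**The concern.** In a Cox model stratified by site, each death is compared only with patients still at risk at the same site. If those patients are all in one arm, the death says nothing about treatment. With 29 strata this happens often: 256/29 ≈ 8.8 randomised patients and 191/29 ≈ 6.6 deaths per site. An event count derived without strata therefore promises more power than the specified test has. At stake is the chance of missing a true hazard ratio of 0.67: the plan puts it at 20%, whereas at 191 deaths it would be about 30%.

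**Working it through.** **1. Reproduce the plan's figure.** Inputs from the Sample size section: one-sided 2.5% (z = 1.960), 80% power (z = 0.842), medians of 12 and 8 months, so HR = 8/12 = 2/3 under exponential survival.

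Schoenfeld, 1:1, no strata: d = 4(1.960 + 0.842)² / (ln 2/3)² = 190.97, i.e. 191. This matches exactly. (HR = 0.67 taken literally gives 196.)

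Patients: with 36 months of uniform accrual and 12 of follow-up, the probability of death is 0.790 (median 12) and 0.892 (median 8), mean 0.841. Then 191/0.841 gives 228, against 230 stated, and 230/0.9 gives 256. The plan's numbers are thus reproduced without any term for site.

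**2. Simulate the specified test.** 4,000 trials per scenario (Monte Carlo error about 0.7 points): exponential survival with medians 12 and 8, 36-month accrual, 29 sites, cut at the 191st death, Cox model stratified by site with sex as covariate, Wald test at one-sided 2.5%. Not in the documents, hence assumed: block lengths (2/4/6 within site and sex), equal numbers of each sex, no sex effect, the site sizes, and the standard deviation (SD) of the site log-hazard.

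| Patients | Site sizes | Site SD | Power, stratified | Power, unstratified |
|---|---|---|---|---|
| 230 | equal | 0 | 69.5% | 78.9% |
| 230 | proportional to 1/√rank | 0.3 | 68.5% | 75.3% |
| 230 | proportional to 1/rank | 0 | 72.6% | 80.5% |
| 230 | 3 sites hold 60% | 0.3 | 72.6% | 77.2% |
| 256 | equal | 0 | 71.1% | 78.8% |
| 256 | 3 sites hold 60% | 0 | 71.4% | 78.9% |

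Over all 16 combinations of these settings, stratified power is 69–73%. About 160 to 165 of the 191 deaths are informative. Under the null, the stratified test rejects in 2.4% of trials.

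**3. Check by hand.** The mean standard error of the log hazard ratio is 0.147 unstratified and 0.162–0.166 stratified. Power ≈ Φ(0.405/SE − 1.960):
- SE 0.147: Φ(0.80) ≈ 79%
- SE 0.162: Φ(0.54) ≈ 71%
- SE 0.166: Φ(0.48) ≈ 68%

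**4. Allow for the planned follow-up of all 256.**
- 36 + 12 months, no dropout: 256 × 0.841 ≈ 215 deaths, power 75%.
- 36 + 12 months, 10% dropout: about 207 deaths, power 73%.
- Slower accrual: the Study status section reports 233 randomised from October 2022 to 16 June 2026, about 44 months. At that rate 256 takes 44 × 256/233 ≈ 48 months (an extrapolation). With 48 + 12 months, 213–224 deaths accrue and power is 75–77%.

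**5. What 80% would take, and what pooling gives.** The site-stratified test reaches 80% at about 230 to 235 deaths (simulated with 290 patients). With 10 equal strata in place of 29, power at 191 deaths is about 75–77%.

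**The case against.** **Analysing by a randomisation factor is conventional, and stratification needs no common baseline hazard across sites.** This stands. There is no bias and no inflation of type I error. The point is only that the event count does not allow for the chosen model.

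**A pooling rule may exist in the full protocol or SAP, which are not shown.** It may, and it would reduce the loss. But the article defines the population-level summary of its primary estimand by the site-stratified model, and that model does not have the stated power at the stated deaths.

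**The cut-off is a date, not the 191st death.** This stands in large part. A reader might infer that the trial simply has 70% power. The documents do not support that as a flat statement, because 256 patients are to be followed for 12 months after the last randomisation, which gives about 73–77%. Longer survival would take back some of this: with the plan's own alternative of 15 and 10 months, 36 + 12 months and no dropout, the mean death probability is 0.780 and 256 patients yield about 200 deaths.

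**Stratification may repay its cost if sites differ.** This stands in part. A reader might infer from the standard errors that the model throws away about a fifth of the information: 1 − (0.147/0.166)² ≈ 22%. That comparison is with an unstratified model when sites do not differ. With a site SD of 0.3 the unstratified test itself falls to about 75–77%, and with 0.4 to about 71–72%, so the net cost of stratifying shrinks. The specified test stays near 70% throughout.

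**Conclusion.** The stated 80% power does not apply to the stated primary test. At 191 deaths and HR 2/3 the test has about 70% power (69–73%); under the planned follow-up of 256 patients, about 73–77%. The shortfall is thus about 7 to 11 points at the stated event count, and about 3 to 7 points under the design as planned.

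That the sample size was unstratified is inferred from the exact reproduction and from the absence of any site allowance; the article does not say so. The power figures assume exponential survival with medians of 12 and 8 months, 29 strata, and no pooling. Site sizes are unknown, but the result hardly depends on them.

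A reader might also infer that the primary model is invalid and must be replaced. The documents do not support that: the test keeps its level, and choosing another model is partly a trade-off.

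**What to change.** 1. **Restate the power** in the Sample size section for the site-stratified model: about 70% at 191 deaths, and about 73–77% with 256 patients under the planned follow-up, with the assumptions on site sizes given. This costs a change of wording.
2. **Preferably, also fix a pooling rule before unblinding.** It should combine small sites into larger strata on blinded counts alone, with the fully site-stratified model kept as a sensitivity analysis. The cost is an amendment to the protocol and SAP, and the assumption that pooled sites share a baseline hazard. Pooling to 10 equal strata recovers part of the loss (75–77% at 191 deaths) but does not reach 80% there, so the restatement is still needed.
3. **Option:** a shared-frailty site effect with sex as covariate. Its downside is the assumption of a common baseline hazard shape across sites. No power figure is offered for it here. It should not be expected to exceed the roughly 80% that the unstratified test has at 191 deaths when sites do not differ, so its power should be simulated before it is adopted.

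The article plans no efficacy interim analysis and reports a blinded study team, so the change can still be made without compromising the trial. No new patients or data are needed.

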### Evidence and need of the trial

Our previous randomized clinical trial DECIDER (for DECItabine, DEacetylase inhibition, Retinoid) was conducted at 27 German trial centres and recruited 200 patients. The trial had a 2 × 2 design investigating the effects of ATRA and the HDAC inhibitor valproate as add-on to DAC. Patients were randomized to the following four treatment arms: DAC (*n* = 47), DAC+valproate (*n* = 57), DAC+ATRA (*n* = 46), and DAC+valproate+ATRA (*n* = 50).

DECIDER was a phase II study with primary endpoint objective best response (complete and partial remission) for a first efficacy assessment of valproate and ATRA add-on. For valproate, no effect was observed with respect to objective best response and overall survival. A beneficial effect of ATRA vs. no ATRA was present with respect to both best response and overall survival. The 1-year overall survival rates were 35% vs. 20%, median overall survival times were 8.2 vs. 5.1 months, hazard ratio (HR) = 0.65, 95% confidence interval (CI) [0.48,0.88], *p* = 0.006, ATRA vs. no ATRA, respectively [6].

The clinical benefit with ATRA was not at the expense of increased toxicity, in line with the safety concerns when combining drugs to treat elderly AML patients. Notably, patients receiving ATRA had a longer time to resistance development, and the survival benefit observed was similar in intermediate and adverse genetic risk groups. Following the positive results of the DECIDER trial, we planned to confirm this effect of ATRA in a placebo-controlled phase III clinical trial. Given the very impressive results in newly diagnosed AML patients receiving VEN in combination with AZA or DAC (see below), we hypothesized that when ATRA is combined with VEN and DAC in a “triplet”, response duration may be prolonged compared to the dual treatment with VEN and DAC, potentially via delay of development of secondary resistance.

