### Study population

The target population of this trial represents patients older than 18 years with AML according to WHO (≥ 20% blasts in the peripheral blood or bone marrow) not qualifying for, or not consenting to, standard remission-induction chemotherapy or immediate allografting. Key inclusion criteria are: patient’s written informed consent; 18 years or older at time of informed consent; patients with primary or secondary AML according to WHO who are not expected to benefit from standard remission-induction chemotherapy; <25.000 leukocytes/µl and performance status ECOG 0, 1, 2. Key exclusion criteria are: Acute promyelocytic leukemia (APL), AML of FAB subtype M3; previous remission-induction chemotherapy for MDS or AML; previous allogeneic stem cell transplantation; previous treatment with DAC, 5-azacytidine, VPA or other DNA-hypomethylating agents, ATRA, venetoclax and other Bcl-2 inhibitors; “low-dose” chemotherapy (e.g. hydroxyurea, cytarabine (Ara-C), melphalan etc.) within four weeks prior to the first ATRA/placebo administration, except for cytoreduction of leukocytosis ≥ 25.000/µl with hydroxyurea or Ara-C as prescribed by the study protocol. Further exclusion criteria are related to general medical conditions or contraindications to administration of investigational product according to Summary of Product Characteristics.

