### Central cytogenetics and molecular diagnostics

Central cytogenetics and molecular diagnostics are being performed in central the reference laboratory of the German–Austrian Acute Myeloid Leukemia Study Group (AMLSG), at the University of Ulm, or at another reference center selected by the site.

For conventional cytogenetic analysis, standard techniques are used and chromosomal abnormalities are described according to the International System for Cytogenetic Nomenclature. The adherence in sending samples to the central laboratory is about 90% of the patients. Molecular genetic characterisation of patient samples is performed according to the European LeukemiaNet Recommendations [22] and include screening for at least the following gene mutations: *NPM1*,* CEBPA*,* FLT3*,* ASXL1*,* RUNX1*,* TP53* and gene rearrangements: *PML::RARA*,* CBFB::MYH11*,* RUNX1::RUNX1T1*,* BCR::ABL1*.

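### The primary survival model is valid but forgoes some precision by leaving out age, ECOG and genetic risk/TP53, which the trial already collects

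*Protocol article*

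**What the plan says.** The Statistical analysis section of the protocol article defines the population-level summary of the primary estimand by one model. It is a Cox regression stratified for site, in which "sex as covariate for adjustment will be used" alongside the ATRA effect, with a one-sided Wald test at 2.5%. Site and sex are also the two stratification factors named under Randomization.

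Three other baseline characteristics are on record:
- Age is an eligibility item under Study population.
- So is "performance status ECOG 0, 1, 2".
- Cytogenetics are analysed, and the molecular work-up includes "screening for at least the following gene mutations", a list that contains TP53 (Central cytogenetics and molecular diagnostics). About 90% adherence is reported for sending samples to the central laboratory, and a site may use another reference center instead.

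On genetic risk, the Evidence and need section reports from the predecessor trial that "the survival benefit observed was similar in intermediate and adverse genetic risk groups".

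On sample size: "The study should have a power of 80% to demonstrate superiority of ATRA vs. placebo", "at one-sided level alpha of 2.5% under the assumption of a hazard ratio of 0.67". Then: "This requires the observation of 191 deaths". The calculation mentions no covariates.

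**The concern.** Sex is the only patient characteristic in the primary model. Age, performance status and genetics are neither balanced by the randomisation nor adjusted for. If they predict death, a model that includes them gives a more powerful test of the treatment effect at the same number of deaths. It also removes the effect of chance imbalance between two arms of about 128 patients (256/2).

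The choice has to be made before unblinding, because covariates added afterwards would not be credible in the primary test. The trial has little power to spare: 191 deaths give 80.0% power only at a hazard ratio of exactly 2/3.

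**Working it through.** **1. The plan's own figures.** Inputs from Sample size: one-sided 2.5%, 80% power, 1:1 allocation, and "A hazard ratio of 0.67 would correspond e.g. to a median OS time of 12 months vs. 8 months".

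- Deaths (Schoenfeld) = 4(1.960 + 0.842)² / (ln HR)². With HR = 8/12 this is 31.40 / 0.1644 = 190.97, so 191. With 0.67 exactly it is 195.8, so 196 deaths, or 79.0% power at 191.
- Probability of death, for exponential survival with rate λ = ln 2 / median, 36 months of uniform accrual and 12 months of further follow-up = 1 − (e^(−12λ) − e^(−48λ)) / (36λ). This gives 0.790 (median 12) and 0.892 (median 8), mean 0.841. Then 191 / 0.841 = 227.2, so about 228 against the stated 230.
- 230 / 0.9 = 255.6, so 256.

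All three figures reproduce, exactly or nearly, without any covariate. The missing adjustment makes none of them wrong.

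**2. Effect of adding the covariates.** Simulation with 230 patients, 29 sites (the number listed in the article), blocks within site and sex, analysis at the 191st death, Cox model stratified by site, Wald test, 6,000 runs per scenario. The Monte Carlo standard error is about √(0.69 × 0.31 / 6000) = 0.6 points. Genetics were missing in 10% and handled by an indicator. The treatment effect was set so that the planned model estimates a hazard ratio near 0.67 (means 0.662 to 0.668), because the article ties its 0.67 to overall medians.

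The prognostic hazard ratios and the prevalences are assumptions. The second column sums them up as the standard deviation (SD) of the log hazard due to the three factors.

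| Assumed HRs: adverse/TP53, ECOG 2, age per SD | SD of log hazard | Planned model | + ECOG, age | + genetics, ECOG, age | Gain from all three |
|---|---|---|---|---|---|
| None | 0 | 69.0% | 69.2% | 69.3% | 0.3 |
| Weak: 1.5, 1.25, 1.1 | 0.22 | 68.5% | 69.6% | 70.3% | 1.8 |
| Moderate: 2.0, 1.5, 1.2 | 0.38 | 68.7% | 70.9% | 73.4% | 4.7 |
| Strong: 3.0, 1.75, 1.35 | 0.60 | 71.0% | 75.4% | 80.7% | 9.7 |

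**3. Type I error.** In the moderate setting with no treatment effect, one-sided rejection was 2.6% for the planned model, 2.8% with all three factors and 2.9% with ECOG and age only. The Monte Carlo standard error is √(0.025 × 0.975 / 6000) = 0.2 points.

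**4. Sensitivity.** With uneven site sizes (assumed), the moderate gain was 70.3% to 74.5%. A second simulation (256 patients, 2,000 runs, treatment HR fixed at 0.667 given the covariates) gave, in the site-stratified model:
- 62.4% to 67.3% with adverse genetics in 40% (HR 2), ECOG 2 in 30% (HR 1.5) and age HR 1.2 per SD;
- 67.8% to 70.4% with hazard ratios of 1.5, 1.3 and 1.15.

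**5. What the gain is worth in deaths.** The number of deaths scales with (1.960 + z_power)². In the moderate case, (1.960 + 0.625)² / (1.960 + 0.487)² = 1.116, and 0.116 × 191 is about 22 deaths. The weak case gives a ratio of 1.042 (about 8 deaths) and the strong case 1.265 (about 51).

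**The case against.** The strongest defence is that nothing here is wrong. The model adjusts for exactly the randomisation factors, which is standard, and the planned 80% never relied on prognostic covariates. That stands, and it limits the point to efficiency.

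Three stronger readings are tempting, and the documents support none of them.

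- **The trial loses power against its plan because of the omission.** A reader who simulates a Cox model without site strata, with the treatment HR fixed at 0.667 given the covariates, gets 71% without and 78% with them. That is not the planned model. It also starts from a weaker overall effect (estimated HR 0.69) than the medians of 12 and 8 months imply. With the overall effect held near 0.67, the planned model has much the same power whether or not the omitted factors matter (69.0%, 68.5%, 68.7%, 71.0%). Its distance from 80% in these runs comes mainly from stratifying by 29 sites: without strata, the sex-adjusted model reached 77% to 78% (78.4%, 77.5%, 77.3%, 78.5%), assuming no true site effect. That is a separate matter.
- **The hazard ratio is biased towards 1.** An HR averaged over covariates differs from one conditional on them even with perfect balance. This is non-collapsibility: two target quantities, not bias in the planned one.
- **The article shows these are the strongest predictors of death.** Its remarks on genetic risk and TP53 mainly concern the treatment effect in subgroups. It gives no prognostic hazard ratio for genetics, ECOG or age.

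The remaining objections concern cost. The estimand's summary is defined by the model, so a change reaches the estimand. 233 patients are already randomised. The 90% describes the sending of samples, and the completeness of TP53 or risk-group results is not stated. These stand as costs. They do not rule the change out: no efficacy interim is planned, the study team is reported as blinded, and unblinded reports went only to the data monitoring committee.

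**Conclusion.** The point holds as a forgone gain in precision, not as an error. Within the planned site-stratified model, adding age, ECOG and genetics is worth about 2 points of power if they are weakly prognostic, about 5 if moderate and about 10 if strong. There is no penalty if they are not prognostic, and the type I error stays near nominal.

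The size rests on assumed prognostic strengths and prevalences, on 10% missing genetics, and on an overall hazard ratio near 0.67. ECOG and age alone, which avoid the missing-genetics problem, give about 1, 2 and 4 points. Low severity: a cheap improvement.

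**What to change.** Before unblinding, prespecify in the primary Cox model, alongside site strata and sex:
- age as a continuous covariate;
- ECOG, 0-1 vs 2;
- genetic risk group with TP53 status, from baseline samples, with a missing category.

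Report the current site-and-sex model as a sensitivity analysis.

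The change needs no further patients, deaths or data collection, but it is more than a wording change in the analysis plan. The population-level summary of the primary estimand must be amended to say that the hazard ratio is conditional on these covariates. The completeness of TP53 and risk-group results, including those from other reference centers, should be checked blind to treatment first. If it proves poor, age and ECOG can be added alone for part of the gain.

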### Study status

Since the start of recruitment in October 2022, a total of 233 patients were randomized in the study until June 16, 2026. Four safety interim analyses were conducted in October 2023, October 2024, September 2025 and April 2026 by the Clinical Trials Unit; the confidential blinded reports were made available only to the coordinating investigator, medical coordinator, and to the DMC. The confidential unblinded reports were made available only to the DMC. Following the DMC recommendation a routine documentation of available platelet and absolute neutrophil count (ANC) was implemented to better monitor hematologic reconstitution. No important safety issues have been observed that would alter the assumed benefit-risk profile. The DMC statements released shortly after corresponding meetings recommended continuing the study as planned, as all DMC members unanimously agreed that at the moment there are no ethical or other concerns on further conduct of the trial.

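### Entering up to 29 sites as a covariate in the response models overstates a true odds ratio of 2 by about a tenth and makes its 95% interval cover too little

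*Protocol article*

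**What the plan says.** The Statistical analysis section of the protocol article analyses both response endpoints with "logistic regression models including, in addition to the effect of ATRA, site and sex as covariates for adjustment". It adds that "the odds ratios (ATRA vs. placebo) will be calculated with corresponding two-sided 95% confidence intervals". It names no conditional likelihood, penalty, random site effect or pooling of small sites.

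The same section handles site differently for overall survival: "A Cox regression model being stratified for site and including, in addition to the effect of ATRA, sex as covariate". Randomization is "stratified by site and by sex, in blocks of variable length in a ratio of 1:1".

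Study design and setting names the sites in a list that begins "Trial sites are located in Aachen, Augsburg, Berlin-Buch, Berlin-Neukölln, Bochum" and runs to 29 locations. Sample size plans 256 patients. Study status reports that "a total of 233 patients were randomized in the study until June 16, 2026".

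**The concern.** The article distinguishes stratifying by site (survival) from entering site as a covariate (response). For a logistic model the distinction matters. A stratified Cox model estimates no site coefficients. A logistic model with site as a categorical covariate estimates one fewer coefficient than there are sites, here up to 28, each from about nine patients. Maximum likelihood then treats those poorly estimated intercepts as if they were known well. The log odds ratio for treatment is pushed away from zero, and its standard error falls short of the estimate's real spread.

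At stake are the adjusted odds ratios and 95% intervals for objective best response and for CR with negative MRD. If ATRA improves response, the error runs in its favour.

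**Working it through.** **The plan's own figures.** The article gives no power or precision figure for the response endpoints, so only the patient number can be reproduced. Deaths for a hazard ratio of 2/3 (8 against 12 months), one-sided 2.5%, 80% power: 4 × (1.960 + 0.842)² / (ln 2/3)² = 191, as stated. Then 230/0.9 = 255.6, rounded up to 256, as stated.

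**Sparsity.** 256/29 = 8.83 patients per site as planned; 233/29 = 8.03 at the reported status. Site coefficients: 29 − 1 = 28.

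**Hand check.** Take a site with N patients, n₁ and n₀ per arm, and m responders. At no treatment effect both likelihoods have the same score for treatment, observed minus expected responders. Their information differs:
- conditional on site: n₁n₀m(N − m) / [N²(N − 1)]
- with a fitted site coefficient: n₁n₀m(N − m) / N³

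The ratio is N/(N − 1). To first order, with equal sites and ignoring sex, the site-coefficient fit multiplies the log odds ratio by N/(N − 1), and its standard error is √[(N − 1)/N] of the true spread.
- N = 8.83: factor 8.83/7.83 = 1.128. A true log odds ratio of 0.693 becomes 0.782, an odds ratio of 2.19. The standard error ratio is √(7.83/8.83) = 0.942. At a true odds ratio of 1 the interval reaches 1.96 × 0.942 = 1.85 true standard deviations, so coverage is about 93.5%.
- N = 8.03: factor 1.142, odds ratio 2.21, standard error ratio 0.936, coverage about 93.3%.

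**Simulation.** 256 patients, 29 sites of equal or skewed size, permuted blocks of 2 or 4 within site by sex. Not in the documents and therefore assumed: control response, true odds ratio, site sizes, and a standard deviation of site effects of 0.4 on the logit scale (0 where marked). There were 8,000 trials per row, or 4,000 in the rows marked no site variation. OR is the exponentiated mean log odds ratio. SE/SD is the mean model standard error over the actual standard deviation.

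| True OR, control response, site sizes | Site coefficients: OR | SE/SD | Coverage | Conditional on site: OR | Coverage |
|---|---|---|---|---|---|
| 2, 60%, equal | 2.21 | 0.940 | 93.0% | 2.01 | 95.4% |
| 2, 60%, skewed | 2.19 | 0.948 | 93.4% | 2.01 | 95.4% |
| 2, 25%, equal | 2.21 | 0.943 | 93.0% | 2.01 | 95.3% |
| 2, 25%, skewed | 2.19 | 0.936 | 93.1% | 2.01 | 95.4% |
| 2, 60%, equal, no site variation | 2.22 | 0.932 | 92.4% | 2.02 | 95.0% |
| 2, 60%, skewed, no site variation | 2.19 | 0.950 | 93.4% | 2.01 | 95.4% |
| 1, 60%, equal | 1.00 | 0.937 | 93.4% | 1.00 | 95.1% |
| 1, 60%, skewed | 1.00 | 0.949 | 94.0% | 1.00 | 95.5% |
| 1, 25%, equal | 1.00 | 0.925 | 93.4% | 1.00 | 94.8% |
| 1, 25%, skewed | 1.00 | 0.927 | 93.4% | 1.00 | 94.8% |

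The error persists without true site differences, so it comes from the number of coefficients and not from the assumed site variation.

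The conditional fit in the table leaves out sex, which had no effect in the simulated data. A separate simulation included sex as covariate in the conditional model and gave an odds ratio of about 2.0–2.05. In that simulation the site-coefficient fit gave about 2.14–2.24, coverage of 91–94% and a standard error about 5–10% too small. A third set (site standard deviation 0.3, control response 65% or 25%) gave medians of 2.16–2.23 and coverage of 92.4–93.5%.

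In the tabulated scenarios, 1.3 to 7.4 sites on average (7.5 to 27.8 patients) had all or no responders. Those sites add nothing to the treatment odds ratio under either model.

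**The case against.** **The fitting method is inferred.** The article says that site is a covariate, not that it enters as unpenalized indicators, and it refers the secondary estimands to the full clinical trial protocol, which is not shown. That document or the SAP may condition on site, penalize, or pool small sites. This stands as a limit on certainty. It does not remove the point: the article does state a model, and its contrast with the site-stratified Cox model makes covariate adjustment the plain reading.

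**The inputs are assumed.** Enrolment by site is not given, so 28 coefficients is an upper figure. If, purely for illustration, 15 sites enrolled all 256 patients, N would be 17.07, the factor 17.07/16.07 = 1.062, and an odds ratio of 2.0 would be estimated near 2.09. This stands too.

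**The size is moderate.** At a true odds ratio of 2 the shift is 0.09 to 0.11 on the log scale against a standard deviation of about 0.32, roughly a third of a standard error. An estimate near 2.2 sits well inside an interval of about exp(0.79 ± 1.96 × 0.30) = 1.2 to 4.0. No test or alpha is stated for these endpoints, so this is not an error rate of a confirmatory claim.

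**Readings that go too far:**
- A reader might infer that any ATRA effect would be overstated. At a true odds ratio of 1 there is no bias.
- A reader might infer that sites with all or no responders make the fit unusable. Their site coefficients run to infinity, but the treatment odds ratio stays finite. The conditional model gains nothing from those sites either, so this does not separate the two.
- A reader might treat a Mantel-Haenszel odds ratio stratified by site as equivalent to the conditional model. It is a different estimator and drops the planned adjustment for sex.
- The intervals are too narrow only for the estimator's own spread. They are wider than the conditional ones (standard error about 0.30 against 0.28 at a true odds ratio of 2).

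**Conclusion.** The point holds with moderate size. Followed as written with up to 29 sites and 256 patients, the response model estimates a true odds ratio of 2.0 at about 2.15–2.25. Its 95% intervals cover about 91–94%, with a standard error roughly 5–10% too small. At a true odds ratio of 1 the estimate is unbiased and coverage is about 93–94%.

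This rests on the plain reading of site as a categorical covariate fitted by maximum likelihood, on most listed sites contributing patients, and on assumed response rates (25–60%), site sizes and site variation. The hand check gives the same direction and size from the patients per site alone.

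A reader might infer that the trial's main conclusion is at risk. The documents do not support that: overall survival is analysed with a site-stratified Cox model, and only the two secondary response endpoints are touched.

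**What to change.** For objective best response and for CR with negative MRD, specify conditional logistic regression stratified by site, with sex as covariate, and report the odds ratio with its two-sided 95% interval as now. This keeps both randomization factors in the analysis and matches the structure of the primary Cox model.

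The cost is one sentence in the protocol or SAP and a small program change. The downside is small: site effects are no longer estimated, and sites where all or no patients respond contribute no information, which is already so under the current model. If the full protocol or SAP already conditions on site, it is enough to bring the article's wording into line.

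The change should be fixed before unblinding. That is still feasible, since the article plans no efficacy interim analysis and states that the study team remained blinded.
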